### Study objectives

Primary objective: To detect thresholds of PRx associated with favourable outcome in PTBI.

Secondary objectives:

Characterise patterns of CPPopt in PTBI as a function of age, severity and character of injury, ICP, etc.Compare the fluctuations in these measured parameters with the outcome.Establish a comprehensive paediatric database of a basic set of high resolution (pulse waveforms resolution) neuromonitoring data including ICP, ABP and ECG.

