### Data collection

ICP will be monitored with an intraparenchymal microsensor inserted into the right (predominately but can be left) frontal cortex and ABP will be monitored in the radial or femoral artery with a zero calibration at the level of the right atrium. The head end elevation is part of the standard international protocol for management for PTBI, and any deviations from this policy in individual cases will be recorded. Full resolution data of routinely monitored physiological parameters in managing PTBI (ICP, ABP, ETCO_2_, SpO_2_ and ECG) will be collected from bed-side monitors. Pulsatile signals (ICP, ABP and ECG) will be recorded with the maximum sampling frequency offered by the bed-side monitors, at least 100 Hz for invasive pressures, and at least 200 Hz for ECG. This will be done using relevant, monitor type specific, data export protocols implemented in the study (ICM+) software running on a bed-side laptop. The same software will be later used for the retrospective analysis of all stored signals. The continuous data collection will be stopped when the patient either starts to wake up or dies and the invasive monitoring is stopped. Apart from general demographics and clinical data, the other data being collected are mechanism and details of injury, relevant history, postresuscitation Glasgow coma scale, initial pupillary size and reactivity, prehospital hypoxia/hypotension/hyperthermia/cardiopulmonary resuscitation, injury and disease severity scores (Paediatric Index of Mortality II score, Injury Severity Score), CT scan findings. We are also collecting: daily laboratory values (haemoglobin, glucose, sodium, lactate), PaO_2_, PaCO_2_ and FiO_2_, PEEP, medical interventions for TBI (positioning, collar, temperature, CO_2_, glucose, hypertonic saline or mannitol, sedation/paralysis, barbiturate coma, anti-seizure medication, use of vasoactive drugs to maintain blood pressure and surgical interventions (haematoma evacuation, elevation of depressed fracture, CSF diversion-external ventricular drainage, new brain imaging, any other relevant event.

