### Outcome measures

The primary outcome will be measured by Glasgow Outcome Scale Extended Paediatric version (GOSE-Peds) at 12-month postinjury against the PRx.

The study will also include the following secondary outcome measures:

GOSE-Peds at 6 months against the PRx.Delta CPP (CPP deviation from CPPopt) against the GOSE-Peds at 6 and 12 months.Rate of severe TBI-related surgical interventions undertaken during the index admission.Mortality (30 days, 6 months 12 months).Length of stay in hospital and rehabilitation.

There is more detailed neuropsychology assessment at 12 months follow-up by using telephone-based interviews and postal questionnaires with parents by using the following tests (child versions will be used where available): Behaviour Rating Inventory for Executive Function (BRIEF), Pediatric Quality of Life Inventory (PedsQL), Strengths and Difficulties Questionnaire (SDQ), Children’s Communication Checklist (CCC), Child and Adolescent Scale of Participation (CASP) and Revised Children’s Anxiety and Depression Scale (RCADS). In addition, with parental permission, school teacher will be contacted for SDQ and BRIEF with postal questionnaires.

Due to the covid-related impact on research, to circumvent the missed follow-ups for the recruited patients:

Where possible, site teams will carry out telephone interview with parents/legal guardian to ascertain child’s neurodevelopmental performance at the first anniversary of child’s head injury for retrospective GOSE-Peds score at 12 months. There is precedence to this approach, especially in children where the developmental milestones/neurodevelopment are judged from memory based on how an individual child performed at different time points in their developmental life.^17–20^
If the child was seen in Acquired Brain Injury/Neurology/Neuro-psychology/Neurodevelopmental clinic at a specific site, the local research team will review the clinic letters/notes to ascertain child’s outcome as close as possible to 12 months from the head injury.

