#### Statistical analysis

Continuous variables will be assessed for normality and expressed as mean (SD) or median (IQR), depending on the underlying distribution of the data. Categorical variables will be reported as counts and proportions. Differences in physiological values between survivors and non-survivors will be interrogated with the Mann-Whitney U test for non-normally distributed continuous variables, Student’s t-test for normally distributed continuous variables and Fisher’s exact test for categorical variables. All tests will be two tailed and unadjusted for multiple comparisons. Spearman rank correlation coefficient (ρ) will be used to see correlations between variables. Identification of critical threshold values of PRx for predicting unfavourable outcome will be performed using iterative χ^2^ tests, as per the method described by Sorrentino *et al*.^21^ To account for any possible confounding effect of the differing periods of monitoring and day post admission on which monitoring starts on outcome associations, ordinal logistic regression analysis will be performed. The independent effect of each continuously monitored variable on GOSE-Peds will be assessed by including the length of monitoring and monitoring commencement day post admission as covariates in the regression models. Where appropriate PRx will be Fisher transformed to remove the <−1; 1> constrain and ensure normalisation of its distribution. The effect of time on PRx will be assessed using repeated-measures analysis of variance with each patient treated as a random effect.

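### The model for the independent effect of PRx on GOSE-Peds names only monitoring length and start day as covariates, so confounding by injury severity and age may be reported as a PRx effect

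*Protocol article*

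**What the plan says.** The protocol article, under Statistical analysis, gives ordinal logistic regression a specific purpose: "To account for any possible confounding effect of the differing periods of monitoring and day post admission on which monitoring starts on outcome associations". It then states what the model will deliver and how: "The independent effect of each continuously monitored variable on GOSE-Peds will be assessed by including the length of monitoring and monitoring commencement day post admission". Both enter the model as covariates, and no further covariate is named for any outcome model. The next sentence turns to Fisher transformation of PRx, so PRx is plainly among the variables meant.

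Other sections bear on this:

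- Outcome measures: "The primary outcome will be measured by Glasgow Outcome Scale Extended Paediatric version (GOSE-Peds) at 12-month postinjury against the PRx".
- Data collection lists baseline prognostic variables: "postresuscitation Glasgow coma scale, initial pupillary size and reactivity, prehospital hypoxia/hypotension/hyperthermia/cardiopulmonary resuscitation", and "injury and disease severity scores (Paediatric Index of Mortality II score, Injury Severity Score), CT scan findings".
- Participant confidentiality and data protection says that month and year of birth are collected to establish age.
- Study objectives gives the only stated analytic use of age and severity: "Characterise patterns of CPPopt in PTBI as a function of age, severity and character of injury, ICP, etc".

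**The concern.** PRx is observed, not assigned. A child with a worse primary injury may have both poorer pressure reactivity and a poorer outcome, whether or not reactivity itself matters. An effect on GOSE-Peds can be called independent only if the model accounts for the main common causes, and the two named covariates describe when and for how long the child was monitored.

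The other PRx-outcome analyses in the section (group tests, rank correlations and the iterative chi-square search for thresholds) include no covariates as described. The regression is therefore the only place where confounding is addressed. The Introduction hopes that thresholds of PRx and CPP will help limit secondary injury and improve outcome. That use needs PRx to carry information beyond the severity already known at admission, and the model as written cannot separate the two.

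**Working it through.** **1. The passages side by side.**

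| Element | What the article gives |
|---|---|
| Claim | an independent effect on GOSE-Peds |
| Confounding addressed | monitoring period and start day |
| Covariates named | monitoring length, commencement day |
| Baseline severity collected | GCS, pupils, prehospital insults, PIM II, ISS, CT findings |
| Age | collected (month and year of birth) |
| Severity or age in an outcome model | none named |

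The article makes the confounding path plausible. The Introduction says that primary injury sets off the secondary insults and refers to autoregulatory dysfunction in severe TBI. The objectives plan to describe CPPopt, which is derived from PRx, by age and severity.

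**2. The number of patients available.** The article states no figure for the adjusted model. Its only sample size, 135, is for an unadjusted comparison of mean PRx: 0.03 (SD 0.13) against 0.10 (SD 0.17), one-sided 5%, 80% power, favourable/unfavourable ratio 0.77, plus losses at an unstated rate. With unequal variances:

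- Unfavourable: (1.645 + 0.842)² × (0.17² + 0.13²/0.77) / 0.07² = 6.18 × 0.0508 / 0.0049 ≈ 64.2, so 65.
- Favourable: 0.77 × 64.2 ≈ 49.4, so 50.
- Total: 115 evaluable. 135 then implies losses of 1 − 115/135 = 14.8%.

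So 135 is consistent with the inputs, though the loss rate cannot be checked. The regression would have about 115 to 135 patients.

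**3. How large the bias could be.** The article gives neither the PRx-severity correlation ρ nor the severity-outcome effect, so both are assumed over a range.

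- Severity S is standard normal; PRx per SD is X = ρS + √(1 − ρ²)·e, with e standard normal.
- Monitoring length and start day are standard normal, independent of everything else.
- Latent outcome = ln(OR) × S + logistic error, cut into five equal groups. PRx has no effect.
- n = 135, two-sided 5% test. There were 400 runs per row up to ρ = 0.2 with OR 2, and 250 runs in later rows.
- The planned model has X, length and start day. The extended model adds S.

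| ρ | Severity OR per SD | Planned: PRx OR | Planned: false positives | With S: PRx OR | With S: false positives |
|---|---|---|---|---|---|
| 0 | 2 | 0.99 | 4.8% | 0.99 | 5.0% |
| 0 | 3 | 1.00 | 5.2% | 1.00 | 5.8% |
| 0.1 | 2 | 1.07 | 6.8% | 1.00 | 4.5% |
| 0.1 | 3 | 1.10 | 10.7% | 1.00 | 5.2% |
| 0.2 | 2 | 1.12 | 12.0% | 0.99 | 5.2% |
| 0.2 | 3 | 1.20 | 22.8% | 0.99 | 6.4% |
| 0.3 | 2 | 1.21 | 23.6% | 1.00 | 6.8% |
| 0.3 | 3 | 1.34 | 47.2% | 1.01 | 5.6% |
| 0.4 | 2 | 1.29 | 35.6% | 0.99 | 3.2% |
| 0.4 | 3 | 1.47 | 66.0% | 1.00 | 6.0% |

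The Monte Carlo standard error of a 5% rate with 250 runs is √(0.05 × 0.95/250) ≈ 1.4 percentage points, so 3% to 7% is in line with nominal.

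**4. A rough sense of scale.** The article's design effect is 0.07 on a root-mean-square SD of √((0.13² + 0.17²)/2) = 0.151. For a binary outcome and normal PRx, the log odds ratio per SD is about 0.07/0.151 = 0.46, an odds ratio near 1.59. The spurious log odds ratios run from ln 1.07 = 0.068 to ln 1.47 = 0.385, or about 15% to 83% of that. The outcome scales differ, so this is orientation only.

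**The case against.** Four points on the other side have weight.

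- **Condensed text.** This is an article of a longer protocol, and its sentence on covariates sits in a paragraph about the monitoring window. A reader might infer that severity adjustment has been ruled out. The article does not say so; it names two covariates and is silent on others. The defence is only partial, because the article does fix a covariate set and attaches the word independent to it. The absence of centre from the model is a different matter: that is silence which an article may leave to the full document, and it is not part of this point.
- **Not the designated primary analysis.** The primary objective concerns thresholds, found by iterative chi-square tests, and the article's strengths section speaks of association. A reader might infer that the main result rests on this regression. The article does not say that. An unadjusted prognostic threshold is a legitimate result if described as one.
- **Monitoring length may carry some severity information.** Recording stops when the child starts to wake or dies and invasive monitoring ends, so length is tied to clinical course. But a short record can follow either a mild or a fatal injury, so it is a poor stand-in. The simulation gives length no such information, and any that it does carry would reduce the bias.
- **The size is assumed.** A reader might infer that confounding will be reported as an autoregulation effect. The documents support only that it may be: at zero correlation there is no inflation. All patients need invasive ICP and ABP monitoring, which may narrow the severity range. The clean result after adjustment also holds by construction, since one perfectly measured variable is the only confounder; real covariates would leave some residual confounding.

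**Conclusion.** The point holds as a mismatch between the claim and the model. The two named covariates do not support an independent effect of PRx, or of any other continuously monitored variable, on GOSE-Peds in this observational cohort.

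Confidence is high on that mismatch and much lower on the amount of bias. The inflation could be negligible or serious, depending on the PRx-severity correlation, the strength of severity as a predictor and how much severity monitoring length happens to capture. None of these can be settled from the article. The concern is milder if PRx is meant only as an unadjusted prognostic marker, but the plan's wording claims more than that. This should be changed before analysis; it does not invalidate the study's design or data.

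**What to change.** - Keep monitoring length and commencement day in the ordinal models and add a short, pre-specified set of baseline covariates already collected: for example age, postresuscitation GCS, pupil reactivity, and one severity score or CT finding.
- Report the two-covariate model as secondary, so that readers can see how far the PRx estimate moves.
- Describe the thresholds from the iterative chi-square tests as unadjusted associations.
- If severity is not added, drop the word independent and say that the effect is adjusted for monitoring window only.

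The cost is analysis-plan wording and about 4 extra degrees of freedom (one each for the four examples, more if any is coded in several categories). With about 115 to 135 patients, intervals may be somewhat wider, which is the reason to keep the list short. No new data are needed.

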## Introduction

Traumatic brain injuries (TBIs) are a major burden to public health with a high incidence and potential long-term consequences.^1^ Incidence of TBI in children ranges from 47 to 280 per 100 000 and are a leading cause of hospital admission and death each year.^2^ Epidemiological studies have demonstrated that the incidence of hospitalisation, fatal brain injury and morbidity is disproportionately higher in children.^3 4^ Despite this, little is known about specific aspects of the paediatric TBI (PTBI) pathology, with most of the knowledge extrapolated from adults. Following head trauma, primary brain injury occurs as a result of the initial trauma. This triggers a cascade of secondary insults in hours to days following primary injury (eg, insufficient blood flow and oxygen supply, low blood pressure, brain swelling, increased intracranial pressure (ICP)), resulting in secondary brain injury. The secondary brain injury plays a significant role in the outcome. Therefore, the focus of standard management of PTBI in paediatric intensive care units (PICUs) is to limit these secondary brain insults.^5^ Current evidence and guidelines suggest use of ICP and cerebral perfusion pressure (CPP; defined as arterial blood pressure (ABP) minus ICP) measurements to guide therapies.^5^ Although there is some consensus on what level of ICP is unacceptably high, the optimal level of CPP is controversial in children. We and others have used advanced monitoring to investigate the association between CPP and clinical outcome^6–8^ and examined means of establishing individualised targets for CPP management, termed ‘CPP Optimal’ (CPPopt), based on analysis of the status of cerebral vascular reactivity, interpreted as a surrogate measure of autoregulation of cerebral blood flow (CBF). Interestingly, CPPopt shows significant variation from the guidelines recommendation, and CPPopt can be different between patients and change over time in each patient.^9 10^ This phenomenon is due to dysfunction and variability of autoregulatory mechanisms in patients with severe TBI that control CBF (and CPPopt).^11 12^ In adults and in our preliminary study in children, we found that the difference between CPP recommended by the guidelines and CPPopt was associated with worsened clinical outcome.^6 9 10^ For this reason, indices of cerebral autoregulation have been recommended to guide management of severe TBI in adults,^13^ but so far there is limited evidence to support their routine use in children.^7 8^

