### Patient recruitment and consent

Each PTBI patient admitted to the recruiting PICU with invasive monitoring of ICP and ABP is considered for recruitment. The research team at each recruiting PICU identifies the patients and sets up high-resolution data collection to the project laptop under an anonymised ID as soon as possible after the patient has been commenced on invasive monitoring and stabilised on PICU. Physiological and clinical data are recorded under this unique study ID. As the acute phase of the project is purely observational and does not involve any therapeutic intervention or change in regular standard care, we take a deferred consent for acute data collection and sharing. This is important to obtain a bias-free sample and ensure capture of early changes in intracranial physiology after head injury. When appropriate, the identified guardian/parent is informed and consented for data sharing and follow-up before the patient is discharged from the hospital. For patients who die before the consent can be obtained, the clinician in charge of patient’s clinical care only (not study team) will access and anonymise data of the deceased patient under his/her clinical care; this anonymised data will then be provided to the study team.

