### Data management and monitoring

Each patient is allocated a unique study ID and all the collected data are anonymised to this ID. Appointed data manager is responsible for monitoring data transfer to Cambridge, for data verification, validation and repackaging, and storing it in the archive location on the server. Full ethical and legal practice is being followed and database will be managed securely under the supervision of data custodian. The project is funded for 5 years (30 June 2023) at present and we will endeavour to get further funding to carry on the data collection and database further in the near future. The data will be stored on a secure server located on a private network behind a tight firewall at the sponsoring institute. We will use the already established system in use for similar larger adult project, CENTER-TBI (https://www.center-tbi.eu/). Briefly, all the physiological time series data collected in each participating site using ICM+ software are stripped of any identifiers and packaged into the HDF5 (https://www.hdfgroup.org/) based format. The file is then uploaded using the Secure Shell Network (SSH) data transfer protocol function of ICM+ to the Cambridge server using public/private key authentication and the username/password distributed in an encrypted format and installed on the ICM+ laptop. The data comes into ‘upload’ folder on that server and is then promptly moved to a staging folder, inaccessible via the SSH connection. The data are then scrutinised for potential problems, artefacts, stripped of any potential identifiers embedded into the annotations, stripped of the data recording date (the timestamps are recorded as relative to the date of ictus, not kept with the data file) and archived permanently. The original data are then removed. All analyses are subsequently done on that preprocessed data. The data are backed up daily, using incremental backup procedure.

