### Statistics

#### Power calculation

The sample size has been calculated assuming a mean (±SD) PRx of 0.03±0.13 in patients with favourable outcome and a mean (±SD) PRx of 0.10±0.17 (SD) for patients with unfavourable outcome (from our previous work).^6^ For a one-sided analysis, using a favourable/unfavourable ratio of 0.77, with 80% power and alpha error of 5%, and allowing for losses (protocol violations, withdrawal of consent or lost to follow-up) the study will require 135 patients. Recruiting 135 patients with severe TBI in 36 months should have been feasible as based on the national audits of PICU (PICAnet report 2015: 188, 210, 211 patients in 2013, 2014 and 2015, respectively, with ICP devices from the 10 UK centres recruiting into the current study) and major trauma (TARN report on 2 years of severe injury in children (2013–2014): 1018 children in 2 years with severe head injury) with an estimated recruitment rate of 5–7 patients per site per year. On the basis of hospital episode statistics and data from the ongoing local severe TBI audit, approximately 5–10 patients with severe TBI are admitted in a medium-sized PICU each year.

However, due to the COVID-19 pandemic, the recruitment has been slow (pause of non-COVID-19 research projects, research staff redeployment to clinical work and lockdowns leading to changes in trauma patterns in children), and the study has been extended until December 2024 in agreement with the sponsor and funding organisation.

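### The start-of-monitoring covariate counts days from admission while signals and outcome are timed from injury, so some confounding by time since injury may remain, by an amount the document cannot fix

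*Protocol article*

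**What the plan says.** The Statistical analysis section of the protocol article gives the reason for the ordinal logistic regression: "To account for any possible confounding effect of the differing periods of monitoring and day post admission on which monitoring starts on outcome associations". It carries this out by "including the length of monitoring and monitoring commencement day post admission as covariates in the regression models" and describes what results as the independent effect of each monitored variable on GOSE-Peds.

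Elsewhere the article counts time from injury:

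- Data management and monitoring: the recording date is removed from the archived signals, and "the timestamps are recorded as relative to the date of ictus, not kept with the data file".
- Outcome measures: the primary outcome is "Glasgow Outcome Scale Extended Paediatric version (GOSE-Peds) at 12-month postinjury against the PRx".
- Introduction, on secondary brain injury: "This triggers a cascade of secondary insults in hours to days following primary injury".

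On when recording begins, Patient recruitment and consent says only that it is set up "as soon as possible after the patient has been commenced on invasive monitoring and stabilised on PICU". The article gives no hours or days for this. It gives no interval from injury to admission, and it does not say whether admission means to hospital or to PICU.

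**The concern.** Two children who start recording on the same day after admission can be at different times since injury, for example if one reached the unit much later than the other. The planned covariate gives them the same value. If PRx and outcome both vary with time since injury, which the Introduction's account of secondary insults makes plausible, that difference stays in the PRx coefficient.

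Unit is a second, separate issue. A count in whole days has little spread if most recordings begin within the first day, and a covariate with little spread adjusts for little.

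At stake is how far the regression coefficient for PRx on GOSE-Peds can be read as independent of the timing of monitoring.

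**Working it through.** **The plan's own figure.** No figure in the article depends on this covariate. The only computed design figure is the 135 patients, from "assuming a mean (±SD) PRx of 0.03±0.13 in patients with favourable outcome" and 0.10±0.17 in those with unfavourable outcome, one-sided 5% alpha, 80% power and a ratio of 0.77. With unequal SDs:

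- unfavourable: (1.645 + 0.842)² × (0.17² + 0.13²/0.77) / 0.07² = 64.2, so 65
- favourable: 0.77 × 64.2 = 49.4, so 50

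The total is 115 before losses. Reaching 135 implies a loss of 1 − 115/135 = 14.8%. The loss rate is not stated, so 135 is consistent with the inputs but not strictly reproducible. Nothing in this calculation uses the start of monitoring.

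**Set-up for the covariate (all assumed).** Let A be hours from injury to admission, M hours from admission to monitoring, and T = A + M. A and M are independent and exponential, with means a and m. PRx and outcome each equal 0.5 × T/SD(T) plus independent standard normal noise, with no true PRx effect. Length of monitoring is not in the model.

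**Formula.** The crude slope is 0.25/(1 + 0.25) = 0.20, all of it bias. After adjusting for a covariate that leaves a fraction v of the variance of T unexplained, the slope is 0.25v/(1 + 0.25v). The share of bias left is therefore 1.25v/(1 + 0.25v).

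- Hours from admission: v = a²/(a² + m²).
- Whole days from admission: with q = exp(−24/m), the day count has variance q/(1 − q)², and v = 1 − 576 × q/(1 − q)² / (a² + m²).

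**Worked examples, whole days from admission.**

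- a = 12, m = 12: q = 0.135, variance 0.181, v = 1 − 104.3/288 = 0.638, share = 0.797/1.159 = 69%.
- a = 1, m = 12: v = 1 − 104.3/145 = 0.281, share = 0.351/1.070 = 33%.
- a = 2, m = 24: q = 0.368, variance 0.921, v = 1 − 530.3/580 = 0.086, share = 0.107/1.021 = 10.5%.

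Simulation with 200,000 children per setting gave 68%, 33% and 9%. Its error is about 1/√200,000 = 0.0022 on the slope, or roughly 1 percentage point of the 0.20, so the two agree.

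**Share of confounding bias left (simulated).**

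| Mean A (h) | Mean M (h) | Hours from admission | Day from admission (plan) | Day from ictus |
|---|---|---|---|---|
| 1 | 12 | 1% | 33% | 31% |
| 2 | 12 | 2% | 34% | 29% |
| 2 | 24 | about 0% | 9% | 8% |
| 4 | 4 | 56% | 96% | 81% |
| 4 | 8 | 25% | 66% | 48% |
| 8 | 8 | 56% | 79% | 34% |
| 12 | 12 | 55% | 68% | 16% |
| 24 | 24 | 56% | 60% | 6% |

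Over the full grid (A mean 1 to 24 h, M mean 4 to 24 h), the planned covariate leaves 9% to about 100%. Changing the origin alone recovers about 1 to about 91 percentage points; the 91 is at A = 24 h, M = 4 h, where 100% falls to 9%.

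**Origin and unit separated.** At A = 1 h, M = 12 h, hours from admission leave 1% and days from admission 33%, so whole-day coding causes nearly all the residual. At A = M = 12 h, hours from admission still leave 55% while days from ictus leave 16%, so the origin dominates.

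**Spread of the day count.** The proportion with day 0 is 1 − exp(−24/m): 63% at m = 24 h, 86% at 12 h, 95% at 8 h and 99.8% at 4 h. These follow from the assumed delays, not from the article.

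**The case against.** The strongest objection is that the article does not claim to adjust for time since injury. It names the differing monitoring periods and the day post admission as the confounders. A reader might infer that the covariate is meant to remove confounding by time since injury and that results will be reported as adjusted for it. The text does not say so; that aim is only an inference from the clocks used elsewhere. This part of the objection stands.

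A reader might also infer that most of the confounding survives, or that nearly every child will have day 0. Neither is supported. Recording waits for invasive monitoring to begin and for stabilisation, with no times given, and the stated rationale itself expects the start day to vary. At 9% most of the bias is gone; at 96% almost none is.

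Nor should it be inferred that hours from ictus would remove all the bias. In such a model time since injury is the only confounder, so that result is built in. Hours are also not shown to be held: the article says "the timestamps are recorded as relative to the date of ictus", which is a date, and lists no injury time among the data collected.

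Finally, the reach is limited. The primary objective, the PRx threshold, is pursued by iterative chi-square tests that do not use this covariate, and exact coding may be settled in the full protocol.

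What the objection does not remove is that the article itself specifies a covariate counted from admission, gives no reason for the change of origin, and holds signals from which a start day relative to ictus appears derivable.

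**Conclusion.** The point holds as a cheap improvement to the supporting ordinal regression. The covariate ignores variation in the injury-to-admission delay and, in whole days, may separate children poorly, so some confounding by time since injury can remain.

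Its size cannot be determined from the document. The range of about 9% to about 100% rests on assumed exponential, independent delays, linear models and time since injury as the only confounder. The choice of origin matters little when admission soon follows injury and a good deal when that delay varies as much as the delay from admission to monitoring. Days from ictus left less bias than days from admission in every setting run, but the smallest gaps are about 1 point and should not be relied on. The model also counts elapsed 24-hour days; calendar dates would be coarser.

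**What to change.** In the Statistical analysis section, make the start-of-monitoring covariate the time from ictus to start of recording, in one unit for all children: days from the ictus date, or hours only if injury time is recorded throughout. Mixing hours for some children with days for others would put two precisions into one term.

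Keep day post admission as a sensitivity analysis, since it may carry separate information such as late deterioration, and state whether admission means hospital or PICU.

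The cost is a change of wording and one extra model. Injury time may be uncertain for some children. The threshold search and the sample size do not change.
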